# Simultaneous comparison of depth of sedation performance between SedLine and BIS during general anesthesia using custom passive interface hardware: study protocol for a prospective, non-blinded, non-randomized trial

**DOI:** 10.1186/s12871-021-01326-5

**Published:** 2021-04-06

**Keywords:** Bispectral index (BIS), Patient state index (PSI), SedLine, Processed electroencephalogram (EEG), Depth of anesthesia, Depth of sedation, Brain function monitoring, Burst suppression state, Electromyography (EMG)

## Abstract

**Background:**

Intraoperative brain function monitoring with processed electroencephalogram (EEG) indices, such as the bispectral index (BIS) and patient state index (PSI), may improve characterization of the depth of sedation or anesthesia when compared to conventional physiologic monitors, such as heart rate and blood pressure. However, the clinical assessment of anesthetic depth may not always agree with available processed EEG indices. To concurrently compare the performance of BIS and SedLine monitors, we present a data collection system using shared individual generic sensors connected to a custom-built passive interface box.

**Methods:**

This prospective, non-blinded, non-randomized study will enroll 100 adult American Society of Anesthesiologists (ASA) class I-III patients presenting for elective procedures requiring general anesthesia. BIS and SedLine electrodes will be placed preoperatively according to manufacturer recommendations and their respective indices tracked throughout anesthesia induction, maintenance and emergence. The concordance between processed EEG indices and clinical assessments of anesthesia depth will be analyzed with chi-square and kappa statistic.

**Discussion:**

Prior studies comparing brain function monitoring devices have applied both sensors on the forehead of study subjects simultaneously. With limited space and common sensor locations between devices, it is not possible to place both commercial sensor arrays according to the manufacturer’s recommendations, thus compromising the validity of these comparisons. This trial utilizes a custom interface allowing signals from sensors to be shared between BIS and SedLine monitors to provide an accurate comparison. Our results will also characterize the degree of agreement between processed EEG indices and clinical assessments of anesthetic depth as determined by the anesthesiologists’ interpretations of acute changes in blood pressure and heart rate as well as the administration, or change to the continuous delivery, of medications at these timepoints. Patient factors (such as burst suppression state or low power EEG conditions from aging brain), surgical conditions (such as use of electrocautery), artifacts (such as electromyography), and anesthesia medications and doses (such as end-tidal concentration of volatile anesthetic or hypnotic infusion dose) that lead to lack of agreement will be explored as well.

**Trial registration:**

Clinical Trials (ClinicalTrials.gov), NCT03865316. Registered on 4 February 2019 – retrospectively registered. Sponsor: Masimo Corporation.

## Background

At present, the end target organ of action for anesthetic agents – the brain – is not routinely monitored given the unclear correlations of brain function monitoring devices in all clinical settings, uncertain benefits in preventing accidental awareness under general anesthesia, variable responses to individual anesthetic agents, and the impact of artifacts [1–3]. Analyses of raw electroencephalogram (EEG) data have characterized anesthetic induction, maintenance, and emergence with specific waveforms and patterns [4]. However, each anesthetic medication produces a unique, but complex, signature on the EEG that must be considered in real-time [5, 6]. At present, routine EEG interpretation during general anesthesia remains impractical given lack of standardized training in this competency and variable support in the medical literature.

Anesthetic overdose, as indicated by burst suppression of the EEG, has been associated with postoperative delirium and increased mortality [7–9]. Anesthetic underdose may risk accidental awareness during general anesthesia and subsequent long-term morbidity, including posttraumatic stress disorder [10–12]. The ideal end-tidal concentration of volatile anesthetic or hypnotic infusion dose for a patient under general anesthesia is dynamic and depends on innumerable patient factors, medications, and clinical situations. Because a complete anesthetic includes amnesia, analgesia, and akinesia, quantifying anesthetic depth is a convoluted, multifactorial estimation. Acute changes, or no changes, in blood pressure and heart rate in response to noxious stimuli currently serve as the primary guide to intraoperative anesthetic management even though vital signs are known to be unreliable indicators of anesthetic depth and are commonly influenced by analgesia and intraoperative events [13].

EEG waveforms can be summarized and translated into dimensionless values over time with proprietary algorithms to offer a simplified, continuous scale of consciousness, thus presenting an additional tool for clinicians to guide attempts to quantify anesthetic depth without the need to interpret raw EEG data [14]. While remaining blind to the mathematical methods or Fourier transform on which the proprietary algorithms are based, clinicians can analyze these processed EEG indices in response to various medications and clinical situations in real-time. Differences in proprietary algorithms between devices may yield disagreements during electromyography (EMG), electrocautery, low power EEG conditions from aging brain, or across anesthetic depth ranges. At present, no individual brain function monitoring device has been shown to be substantially superior.

The Bispectral index (BIS) monitor was the first depth of anesthesia device to analyze the phase and power of EEG frequency bands through a proprietary algorithm, thus distinguishing it from competitors [15, 16]. In contrast, the more recently introduced SedLine monitor provides a patient state index (PSI) to quantify anesthetic depth by analyzing the spatial and temporal gradients of EEG frequency bands in the anterior-posterior dimension [17]. The accuracy and clinical utility of these two monitors depend on various factors including EMG, electrocautery, patient age, and pre-existing neurological disorders [18–21]. Therefore, despite their appeal, processed EEG data must be interpreted with caution.

Prior investigators have attempted to simultaneously compare the performance of BIS and PSI by placing multiple sensors on subjects’ foreheads [22, 23]. However, with limited space and common sensor locations between the two devices, it is not possible to place both commercial sensor arrays according to the manufacturer’s recommendations. Non-standard lead placement compromises the interpretation of the comparisons thus made. We hypothesized that processed EEG indices from BIS and SedLine monitors can be measured simultaneously using individual electrode placement and a custom designed interface box to combine and split signals, thus allowing performance to be compared across a broad range of anesthetic depths. This data collection system allows us to investigate the concordance between these monitors and real-time clinical assessments of anesthetic depth and analyze the actions of the anesthesiologists in response to acute changes in blood pressure and heart rate.

## Methods

### Study design and setting

This data collection system will be used in a prospective, non-randomized, non-blinded trial approved by the Institutional Review Board (IRB) at the University of California, Davis. The anesthesia providers responsible for the intraoperative care of included patients will be blinded to the processed EEG indices and not permitted to utilize these indices to guide the anesthetic management. Any adverse events observed throughout the trial will be communicated with the IRB and sponsor.

### Study population

Written informed consent will be obtained from all study participants or their surrogates. We plan to enroll up to 100 patients in this study to observe whether or not the custom built passive interface hardware allows for accurate, simultaneous comparison of BIS and SedLine devices. Because of the absence of any comparative data, this sample size was arbitrarily chosen so that the study participants will include a heterogenous group of surgeries, comorbid conditions, and patient demographics. All patients will meet the following criteria:

#### Inclusion criteria

Patients aged 18 years or olderAmerican Society of Anesthesiologists’ (ASA) status I-IIIEnglish-speakingScheduled for surgical or non-surgical procedures requiring general anesthesia

#### Exclusion criteria

Any deformities or devices that may prevent application of EEG sensors to the patient’s foreheadDevelopmental delayOther conditions for which the patient is otherwise deemed not suitable for the study at the discretion of the investigator. Unsuitable conditions include inadequate forehead space to allow for all electrodes to be properly positioned. Patients will also be excluded based on chronic medical conditions that may impact EEG recordings (such as a history of frontal sinus surgery or epilepsy).Surgeries in the lateral or prone position, which may alter the impedance of the electrodes and make it difficult for the investigators to troubleshoot.

### Study devices

The following devices will be utilized in this protocol:
FDA-cleared Root™ Rainbow Technology Multi-Function Docking Station (Masimo Corporation)FDA-cleared SedLine patient module (Masimo Corporation)FDA-cleared BIS system (Medtronic/Covidien)FDA-cleared 3rd party EEG/ECG sensorsLaptop computer with PulseOX Automatic Data Collection (ADC) and Rugloop (data collection software)Custom built passive interface box to facilitate simultaneous connection of BIS and SedLine monitors; this interface has no active electronics

### Processed EEG setup

After the sub-investigator, principal investigator, research coordinator, or other participating site staff obtains written informed consent from included participants on the day of surgery, the preoperative baseline heart rate and blood pressure will be collected. The patient’s age, weight, race, ethnicity, and significant co-morbid conditions will be recorded on a case report form (CRF). The forehead skin of included patients will be prepared with 70% alcohol wipes to decrease impedance for 11 third-party EEG sensors (Kendall 1050NPSM Neonatal ECG Electrodes). BIS ground channel (BIS GND) and sensor electrodes will be placed in locations according to the manufacturer’s recommendations and labelled right temple (RT), right eye (RE), left temple (LT), and left eye (LE). SedLine sensor electrodes will be similarly placed according to the manufacturer’s instructions and include 4 active channels (R1, R2, L1, and L2) and 1 ground channel (CB) [24]. The BIS and SedLine electrode arrays share an additional common reference channel (CT). The final locations of these EEG sensors are shown in Fig. 1.

**Fig. 1 Fig1:**
[figure not shown]
Proper placement of 11 EEG electrodes to allow for simultaneous recording of BIS and PSI indices

The patient will then be transported to the operating room where the EEG sensors will be connected to a custom-built passive interface box. This box contains only resistors and wires and no active electronics. Connections extend from this box to the BIS and SedLine modules as demonstrated in Fig. 2. BIS and SedLine data are recorded using Rugloop (2018 version 10.10) and Masimo Automated Data Collection (proprietary, 2017 version 10.4) software, respectively. The data collection system is shown in Fig. 3.

**Fig. 2 Fig2:**
[figure not shown]
Custom interface adapter to allow for concurrent connection of EEG sensors to both BIS and SedLine modules

**Fig. 3 Fig3:**
[figure not shown]
Mobile data collection station showing laptop computer with data collection software; custom interface adapter with ports for connection to sensory electrodes and cables to BIS and SedLine monitors; BIS monitor; and SedLine Root monitor

Prior to beginning data collection, each sensor will be checked to ensure that impedance of each channel is less than or equal to 15 kohms (kiloohms). Sensors with an impedance greater than 15 kohms will be permissible only if the EEG waveform is deemed to be of acceptable quality. Unacceptable EEG waveform quality will prompt application of additional gel to reduce impedance or sensor replacement. After a successful impedance test is recorded, impedance testing will be disabled, and data collection initiated.

### Data collection

Data collection will begin with a baseline set of BIS and PSI indices. Once recorded, general anesthesia will be induced with medications and doses chosen by the intraoperative anesthesia care team and documented in the electronic medical record (EMR). The depth of sedation during induction will be measured, at least, every minute using the Modified Observers’ Assessment of Alertness/Sedation (MOAAS) scale until the patient loses the eyelash reflex and achieves a score of 0. Two MOAAS scores can share the same timepoint if the patient achieves a new score less than 1 min from the prior score. The following descriptions of MOAAS scores will be used: 0 does not respond to pain; 1 does not respond to mild prodding or shaking; 2 responds after mild prodding or shaking; 3 responds after calling loudly or repeatedly; 4 responds slowly to voice with normal tone; 5 responds readily to voice with normal tone. Times indicating start of anesthesia induction, endotracheal intubation, surgical incision, and the start of electrocautery will also be recorded. Electronic, time-stamped documentation of intravenous medication doses in the EMR by the anesthesia provider will allow for retrospective review of their effects on raw and processed EEG data by investigators. Similarly, end-tidal concentrations of volatile gases will be automatically recorded in real-time within the patient’s EMR throughout the entire surgery.

Throughout the course of the surgical procedure, timepoints with acute changes of ±20% in blood pressure or heart rate from baseline values will be recorded. At these timepoints, an investigator will question the anesthesia provider regarding the suspected cause for each acute change as “Light Anesthesia”; “Deep Anesthesia”; “Volume Status”; or “Other.” The anesthesia provider will not be limited in responses for “Other.”

At the end of the surgical procedure, timepoints indicating incision closure, emergence from anesthesia, tracheal extubation, and return of consciousness will be recorded. During emergence, MOAAS will be measured every minute until the patient achieves a score greater than or equal to 4. Sensors will be removed prior to patient transport to the post-anesthesia care unit (PACU). A timeline of events and experimental recordings are shown in Fig. 4.

**Fig. 4 Fig4:**
[figure not shown]
Timeline of Events and Experimental Recordings

Raw and processed EEG data will be organized according to the patient’s unique study identification number. Record of medication administration will be stored in the EMR and accessible to investigators by searching the patient’s medical record number (MRN). Preoperative patient demographics, vital signs, ethnicity, race, ASA status, description of surgical procedure, pre-existing diseases, surgical position, MOAAS scores, event timepoints, anesthesiologists’ assessments, and general comments will be written on the CRF, which will then be scanned, and electronically stored in a password-protected, encrypted N: drive.

### Monitoring

Data monitoring will occur regularly with and without sponsor involvement to ensure that data collection is accurate and complete. The investigators and sponsor of this protocol will have access to interim analyses and decide to amend the protocol or terminate the trial, if applicable. Furthermore, trial conduct will be regularly audited by the sponsor, and amendments will be communicated with the IRB.

### Primary outcomes

This protocol’s primary endpoint is to establish the concordance, or extent of agreement, between the processed EEG indices from BIS and SedLine monitors and the real-time clinical assessments of anesthetic depth by clinicians during “Deep Anesthesia Events” and “Arousal Events.” Investigators will retrospectively review the EMR to identify interventions made by the anesthesia providers during 10 min surrounding (5 min before and after) periods of burst suppression noted on raw EEG or acute changes in blood pressure or heart rate ± 20% from baseline values. The performace of processed EEG indices surrounding periods of burst suppression on raw EEG will also be analyzed.

Clinically identified possible “Deep Anesthesia Events” are defined as acute decreases in blood pressure or heart rate greater than or equal to 20% from the patient’s preoperative baseline values. The clinical diagnosis of “Deep Anesthesia” coupled with any of the following on the raw EEG, BIS or SedLine monitors indicates agreement: burst suppression on raw EEG, processed EEG index value consistent with a deep anesthesia state per manufacturer recommendations (below 40 for BIS or below 30 for SedLine), or an acute decrease in the processed EEG index by 10 over the same index 5 min prior to the event. The actions of the anesthesia providers will also be examined during these timepoints, in particular the administration of hypnotic (such as propofol or volatile agent) or analgesic medication.

Clinically identified possible “Arousal Events” are defined as acute increases in blood pressure or heart rate greater than or equal to 20% from the patient’s preoperative baseline values. The clinical diagnosis of “Light Anesthesia” coupled with any of the following on the BIS or SedLine monitors indicates agreement: processed EEG index value that signifies inadequate anesthesia per manufacturer recommendations (greater than 60 for BIS or greater than 50 for SedLine), or an acute increase in processed EEG index by 10 over the same index 5 min prior to the event. The actions of the anesthesia providers will also be examined during these timepoints, in particular the administration of hypnotic (such as propofol or volatile agent) or analgesic medication.

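### The Deep Anesthesia agreement rule counts raw-EEG burst suppression as index agreement, and neither agreement rule states that BIS and SedLine are scored separately

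*Protocol article*

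**What the plan says.** The title announces a "Simultaneous comparison of depth of sedation performance between SedLine and BIS during general anesthesia". The Primary outcomes section sets the endpoint as the concordance "between the processed EEG indices from BIS and SedLine monitors and the real-time clinical assessments of anesthetic depth by clinicians".

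The same section then gives the scoring rules:

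- **Deep Anesthesia Events.** The clinician's diagnosis "coupled with any of the following on the raw EEG, BIS or SedLine monitors indicates agreement". The list begins with "burst suppression on raw EEG, processed EEG index value consistent with a deep anesthesia state per manufacturer recommendations". The cut-offs for the index value are set at "below 40 for BIS or below 30 for SedLine". The last sign on the list is "an acute decrease in the processed EEG index by 10 over the same index 5 min prior to the event".
- **Arousal Events.** The clinician's diagnosis "coupled with any of the following on the BIS or SedLine monitors indicates agreement". The signs are a BIS value above 60, a SedLine value above 50, or a 10-point rise. There is no raw-EEG sign.

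The section also promises a further analysis: the performance "of processed EEG indices surrounding periods of burst suppression on raw EEG will also be analyzed". The Statistical analysis section applies a chi-square test to the percentage of agreement and adds kappa with its standard error. It does not define an agreement variable for each device.

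**The concern.** There are two separate problems.

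1. **The Deep rule does not match its endpoint.** The endpoint concerns processed indices. Burst suppression read from the raw trace is the output of neither index, yet it is enough by itself to score agreement. The primary count therefore includes events in which no index agreed with the clinician.

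2. **The unit of scoring is left open.** Read literally, a sign on either monitor satisfies the rule, and each event gets a single agreement value. One device is then credited with what the other showed, and the difference between devices is zero by construction.

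At stake is whether the primary endpoint, as worded, measures index performance and can show a difference between BIS and SedLine.

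**Working it through.** The documents state no agreement rate, so there is no figure to reproduce. All rates below are assumptions, chosen to show a range.

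**Step 1. One event against the rule.** Take a clinician diagnosis of deep anesthesia with burst suppression on the raw EEG, BIS 45, PSI 45 and no 10-point fall. BIS 45 is not below 40, PSI 45 is not below 30, and the change sign is absent, so neither index supports the clinician. The rule still scores agreement through the raw-EEG sign. This follows whether the devices are pooled or scored one at a time.

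**Step 2. How far the pooled Deep rule exceeds a single device's own rule.** Let L be the chance that a device is in its deep range, D the chance of a 10-point fall and b the chance of burst suppression. Both devices have the same L and D, and L, D and b are independent.

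- Own rule: s = 1 − (1 − L)(1 − D)
- Pooled rule, independent devices: 1 − (1 − s)²(1 − b)
- Pooled rule, fully concordant devices: 1 − (1 − s)(1 − b)

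| L / D / b | Own rule s | Pooled, independent | Pooled, concordant |
|---|---|---|---|
| 20% / 5% / 2% | 1 − 0.80×0.95 = 24% | 1 − 0.76²×0.98 = 43% | 1 − 0.76×0.98 = 25.5% |
| 30% / 10% / 5% | 1 − 0.70×0.90 = 37% | 1 − 0.63²×0.95 = 62% | 1 − 0.63×0.95 = 40.2% |
| 40% / 15% / 10% | 1 − 0.60×0.85 = 49% | 1 − 0.51²×0.90 = 77% | 1 − 0.51×0.90 = 54.1% |

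The excess is about 19, 25 and 28 points with independent devices and about 2, 3 and 5 points with concordant ones. If, in addition, burst suppression occurs only when the indices are in their deep range, it adds no events and the excess is zero.

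**Step 3. What a shared flag does to the device contrast.** Suppose that, among events the clinician called deep, the BIS sign is present in 60% and the SedLine sign in 40%. Scored on their own indices, the devices differ by 20 points. The shared flag gives one figure. With independent signs and b = 5% it is 1 − 0.40×0.60×0.95 = 77%. Across a latent correlation of 0 to 0.8 between devices and b of 5% to 40%, it runs from 65% to 86%. With the same sign rates for Arousal, where b plays no part, it runs from 63% to 76%. The device difference is 0 throughout.

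A simulation of 400,000 events, without a raw-EEG sign, shows the same for kappa. One informative device (own kappa about 0.49) paired with a pure-noise device (about 0.00) gives a single pooled kappa of about 0.29. With own kappas of about 0.49 and 0.23, the pooled kappa is about 0.42 whichever device is the better one.

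**Step 4. The per-device reading, with the raw-EEG sign kept.** If burst suppression is independent of the index signs, a device with own rate p scores 1 − (1 − p)(1 − b). The difference between devices becomes (p_BIS − p_SedLine)(1 − b):

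- b = 2%: 20 × 0.98 = 19.6 points
- b = 5%: 62% against 43%, 19 points
- b = 10%: 20 × 0.90 = 18 points
- b = 20%: 68% against 52%, 16 points
- b = 40%: 76% against 64%, 12 points

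At b of 2% to 10%, the range used in Step 2, the dilution is small.

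**The case against.** The strongest reply is that pooling is one reading of the text and not a stated rule. The cut-offs are device-specific, the change is measured within the same index, and a percentage of agreement tested by chi-square is natural if each monitor has its own percentage. An article may also leave the coding of a per-device variable to the full protocol or analysis plan. This stands in part: per-device scoring is a fair reading. But neither the Primary outcomes nor the Statistical analysis section states it, and it does not remove the raw-EEG sign from the Deep rule. That sign is written into the endpoint rule, so it is not a detail left for later.

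A reader might go further and infer three things that the documents do not support:

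- **That the trial cannot tell the two devices apart.** This holds for the endpoint on its literal reading, not for the data. The Processed EEG setup section has each index recorded by its own software, so per-device scoring remains possible.
- **That an index's failure to detect burst suppression would be hidden.** The section already plans to analyse index performance around burst suppression. Such misses could be seen there, although they would still count as agreement in the primary figure.
- **That the missing raw-EEG sign in the Arousal rule invalidates a comparison of Deep with Arousal rates.** The two rules do differ in structure, but the article plans no such comparison, and the Background treats burst suppression as a sign of anesthetic overdose.

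The larger figures in Step 2 also need full independence. The two arrays share a reference channel, and the Trial status section reports that the indices appear to move in parallel during induction, so the lower end deserves weight. Kappa is planned to correct for chance agreement, but it cannot separate two devices that share one flag.

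**Conclusion.** The mismatch between the endpoint and the Deep rule holds on any reading: an event missed by both indices can count as index agreement. The shared flag holds on the literal reading only. On that reading the device contrast is zero whatever the true difference; on the per-device reading the contrast survives but is diluted in Deep events, by a factor of 1 − b under independence.

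The size of the inflation cannot be fixed from the documents. Under the assumed rates it is about 19 to 28 points with full independence, about 2 to 5 points with fully concordant devices, and none if burst suppression also always coincides with the deep index range. The case for correcting the rule rests on its wording, not on any one of these figures.

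**What to change.** Reword the agreement definition in the Primary outcomes section:

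- Score each event twice: once for BIS, using the BIS value or BIS change only, and once for SedLine, using the PSI value or PSI change only. Do this for Deep and Arousal events, and report percentage agreement and kappa for each device.
- Remove raw-EEG burst suppression from the index agreement rule. Report it as its own comparator within the burst-suppression analysis already planned: clinician against burst suppression, and the proportion of burst-suppression periods in which each index is in its deep range.

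The clinical thresholds stay as they are. All inputs are already recorded, so the cost is a rewording and a lower stated agreement.

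### The 10-point change criterion does not require its 5-minute reference value to lie after induction, so for events soon after induction the index half of a Deep agreement is fixed in advance

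*Protocol article*

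**What the plan says.** Primary outcomes defines possible Deep Anesthesia Events by "acute decreases in blood pressure or heart rate greater than or equal to 20% from the patient’s preoperative baseline values", and Arousal Events by the mirror-image increases. A clinical diagnosis of Deep "coupled with any of the following on the raw EEG, BIS or SedLine monitors indicates agreement". There are three options for Deep. One is burst suppression on raw EEG. Another is the change criterion, "an acute decrease in the processed EEG index by 10 over the same index 5 min prior to the event". The last is a level criterion, with cut-offs "below 40 for BIS or below 30 for SedLine". For Light there are two options: the change criterion is "an acute increase in processed EEG index by 10 over the same index 5 min prior to the event", and the level criterion has the cut-offs "greater than 60 for BIS or greater than 50 for SedLine". No phase of anesthesia is named in either change rule.

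The Abstract has "their respective indices tracked throughout anesthesia induction, maintenance and emergence". Data collection begins with a baseline pair of indices taken before induction, so an awake value exists for the look-back to reach. The same section places the recording of hemodynamic events over the duration of the surgical procedure, without saying when that begins. Inclusion criteria also admit procedures that are not operations. Statistical analysis plans percentage agreement with a chi-square test, and kappa, with no split by phase.

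**The concern.** The change rule is meant to detect a shift in the index around a hemodynamic event. Soon after induction, the value 5 minutes earlier may be an awake value or one taken while the patient is losing consciousness. The difference then measures induction itself. A patient whose index sits comfortably in the adequate band would be scored as having an index consistent with excessive depth. The event trigger has the same reference problem, because it compares an anesthetized patient with preoperative blood pressure and heart rate. In these minutes both the trigger and the index criterion can be met by an ordinary induction.

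At stake is the meaning of the primary concordance measure. An event scored this way tells the reader about clock time since induction and about how clinicians label early pressure falls. It tells nothing about whether either monitor tracks depth.

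**Working it through.** The plan states no figure that bears on this point (the 100 patients are described as an arbitrary choice), so there is nothing to reproduce. The check uses the protocol's own thresholds.

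**Inputs from Primary outcomes.** Deep levels: BIS below 40, SedLine (PSI) below 30. Light levels: BIS above 60, PSI above 50. The implied adequate bands are BIS 40–60 and PSI 30–50. Change of 10 points, look-back of 5 minutes.

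**Step 1: when does the whole adequate band count as Deep?** A reading *v* meets the change rule if reference − *v* ≥ 10. The hardest case is the top of the band.
- BIS: reference ≥ 60 + 10 = 70.
- PSI: reference ≥ 50 + 10 = 60.

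From those values upward, 100% of in-band readings meet the rule. At a BIS reference of 65, readings 40 to 55 meet it, which is 16 of 21 integer values (76%). Awake index values are not in the text. Over an assumed range of 70 to 97 the share is 100% for both monitors.

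**Step 2: one reading can support opposite labels.** Take a reference BIS of 90 and a current BIS of 65. The fall is 25, so the Deep change criterion is met. The reading is also above 60, so the Light level criterion is met. The same value would support Deep on a pressure fall and Light on a pressure rise.

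**Step 3: the arousal side.** With a BIS reference of 70 or more, a 10-point rise ends at 80 or more, already above 60. With a PSI reference of 60 or more it ends at 70 or more, already above 50. The Light change criterion adds nothing there, and such events are in effect scored on level alone.

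**Step 4: agreement inside an affected window.** Assume a two-by-two table of clinician (Deep or not) against index (supports Deep or not). Let the clinician call a share *q* Deep while the index is always positive.
- Observed agreement = *q*.
- Chance agreement = *q* × 1 + (1 − *q*) × 0 = *q*.
- Kappa = (*q* − *q*)/(1 − *q*) = 0 for any *q* below 1.

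**Step 5: pooled effect, under assumptions.** Suppose that in the other events clinicians call half Deep and the index matches in 70% of each group: agreement 0.70, kappa 0.40. Let a share *f* of all events lie in the affected window. The cells are:
- both positive: (1 − *f*) × 0.35 + *f* × *q*
- clinician only: (1 − *f*) × 0.15
- index only: (1 − *f*) × 0.15 + *f* × (1 − *q*)
- neither: (1 − *f*) × 0.35

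For *f* = 0.2 and *q* = 0.2 these are 0.32, 0.12, 0.28 and 0.28. Agreement is 0.60, chance agreement 0.44 × 0.60 + 0.56 × 0.40 = 0.488, and kappa 0.112/0.512 = 0.22.

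| *f* | *q* | Agreement | Kappa |
|---|---|---|---|
| 0.1 | 0.2 / 0.5 / 0.8 | 0.65 / 0.68 / 0.71 | 0.30 / 0.36 / 0.42 |
| 0.2 | 0.2 / 0.5 / 0.8 | 0.60 / 0.66 / 0.72 | 0.22 / 0.32 / 0.43 |
| 0.3 | 0.2 / 0.5 / 0.8 | 0.55 / 0.64 / 0.73 | 0.15 / 0.28 / 0.43 |

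The pooled result moves down when clinicians seldom call these events Deep and slightly up when they usually do.

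**The case against.** The best defense is the layout of Data collection. Its first paragraph covers induction and uses MOAAS, its second covers hemodynamic events during the procedure, and its third turns to emergence and returns to MOAAS. On a natural reading, intubation and emergence are not scored as Deep or Arousal events at all. Only an event soon after the procedure begins, within about 5 minutes of induction, would reach back to an awake value. The retrospective record review in Primary outcomes does not widen this. It identifies interventions, whereas the clinician's label comes only from real-time questioning. This is also a condensed article whose timeline figure is not shown, and the stated aim covers a broad range of depths.

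Much of that stands, and it narrows the affected set. It does not remove it. The start of the procedure is not tied to incision or to any other recorded time, and incision cannot serve for non-surgical cases. The scoring rule itself is stated with numbers and has no condition on the reference value, so this is more than detail left to another document.

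A reader might infer that the course of anesthesia decides agreement by itself. It does not: the clinician may answer Light, Deep, Volume Status or Other, and a matching label is required. A reader might also infer that emergence is equally affected. Even if emergence events are in scope, the level criterion is met once the index passes 60 or 50, so the change rule adds only rises of 10 or more that end at or below those values.

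**Conclusion.** The point holds in a limited form. The Deep change criterion gives an uninformative score for any event whose look-back reaches BIS 70 or more, or PSI 60 or more, with the current reading in or below the adequate band. In that window kappa is 0 and percentage agreement equals the clinicians' labelling rate.

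It is tempting to conclude that reported agreement is inflated. That would follow if only Deep-labelled events were counted: with 50% agreement elsewhere and 20% of them affected, 0.5 × 0.8 + 0.2 = 60%. But the analysis is of all possible events, defined by the hemodynamic change, and those labelled otherwise then become disagreements. The direction is therefore not established. Nor do the documents show that the two monitors will be made to look alike. The share of affected events, the awake index values and the base agreement are all assumptions here. The defect lies in the primary endpoint's scoring rule and is worth correcting before analysis. It does not call for limiting the whole primary outcome to maintenance.

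**What to change.** Add to the outcome definition that the 10-point change criterion applies only when the 5-minute reference point lies after MOAAS 0 has been reached. Score earlier events on the level criterion alone and, for Deep events, also on raw-EEG burst suppression. State the start and end of the event window, including for non-surgical procedures. Report any events during induction or intubation, or after the recorded start of emergence, as a separate stratum.

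No new data are needed. MOAAS is taken at least every minute during induction, "Times indicating start of anesthesia induction, endotracheal intubation, surgical incision, and the start of electrocautery will also be recorded", and the time of emergence is noted. The cost is a few sentences and a filter on recorded times. The small downside is that fewer events are scored on the change criterion.
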